#### Care Network Participants

Care network participants will be asked to complete questionnaires in the same manner as participants with multimorbidity (ie, online or over the phone, with data captured through REDCap [49,50]). At the beginning of their trial periods, all care network participants will be asked to complete a questionnaire that captures their demographic information; informal caregivers will also be asked to complete the Zarit Burden Interview [51]. At the conclusion of their trial periods, all care network participants will again be asked to complete 2 questions that capture their opinion on how the use of ProACT influenced their care and any burden they may have experienced while using ProACT (ie, measured via the User Burden Scale) [47]. Informal caregivers will also be asked to complete the Zarit Burden Interview [51]; while any formal caregivers, formal care quality assistants (ie, managers of formal caregivers), or health care professionals taking part in the process evaluation may have an additional questionnaire to complete (ie, the ProTransfer questionnaire; see Process Evaluation Methodology section). All questionnaires can be completed online or over the phone, depending upon the participants’ preferences. The full list of key assessment domains and measures is available to view in Table S3 in Multimedia Appendix 2.

At the conclusion of their trial periods, the research teams will also conduct semistructured interviews or focus groups with up to 60 participants in each care network group (ie, with up to 20 participants in each care network group in each country) to collect data on their satisfaction with and attitudes toward the technology, etc. These will likely take place over the phone or online due to trial resource limitations and the anticipated wide geographic spread of care network participants within each country, particularly of informal caregivers. For health care professionals and formal caregivers or formal care quality assistants, these will take place either by phone, online, or at their place of work, depending upon what is most convenient for them. The interviews or focus groups will be audio-recorded and transcribed, and the researchers will subsequently annotate and analyze the collected data.

Finally, care network participants’ system use statistics (eg, data that capture their use of the ProACT CareApp) will be collected continuously throughout their 6-month trial period.

The primary outcomes for informal caregivers include caregiver burden. Other outcomes for all care network participants include the usability, accessibility, and acceptability of, and engagement, satisfaction, and overall experiences with, ProACT.

### Process Evaluation Methodology

Participants with multimorbidity, care network participants, and the clinical triage services and partner organization staff will participate in the process evaluation. For participants with multimorbidity and care network participants, the process evaluation will not result in additional research activities beyond those described in Table 2 and Tables S1 and S2 in Multimedia Appendix 2. However, topics specific to the process evaluation will be included in the interview and focus group protocols for the p-RCT evaluation.

Four types of data will be collected: administrative data, self-report questionnaire data (eg, ProTransfer data), digital analytic data (ie, system use data), and interview data. Table 2 summarizes what data will be collected, from whom, and when. Some of the data listed here will already be collected during the p-RCT (eg, the digital analytics data). For the semistructured interviews or focus groups, up to 60 participants with multimorbidity in each of trial arms 1 and 2 (ie, up to 20 participants in each country), up to 60 individuals in each care network group (ie, up to 20 individuals in each care network group in each country), the clinical triage services, and up to 15 partner organization staff (ie, up to 5 staff in each country) will be asked to participate. Interviews will likely take place over the phone or by online video call. The interviews and focus groups will be audio recorded and transcribed, and the researchers will subsequently annotate and analyze the collected data. The administrative, ProTransfer (questionnaire), and digital analytics data will be captured using electronic means (ie, online).

The outcomes for participants with multimorbidity in trial arms 1 and 2, all care network participants, and the clinical triage nurses include the usability, accessibility, and acceptability of, and engagement, satisfaction, and overall experiences with ProACT; and the way end users (ie, participants with multimorbidity, care network participants, and the clinical triage nurses) use ProACT (eg, to view one’s readings, to set goals, and to consume educational material), how they differ in this regard (eg, to view readings only, to set goals only, or to consume educational material only), and the factors that influence these differences (eg, a participant with multimorbidity’s condition and age).

The outcomes for partner organization staff include the reach, uptake, and fidelity of implementation of ProACT; the usability, accessibility, and acceptability of ProACT; and engagement, satisfaction, and overall experiences with ProACT; and the way organizations implement and deliver ProACT, how they differ in this regard, and the factors underpinning these differences (eg, societal- and organizational-level contextual factors, such as leadership buy-in).

**Table 2 table2:** Process evaluation data collection.

Participants	Administrative data	ProTransfer data	Digital analytics	Interviews or focus groups
Management	✓ (pre)	✓ (pre and post)		✓ (post)
Participants with multimorbidity and care network participants			✓ (ongoing)	✓ (post)
Clinical triage nurses			✓ (ongoing)	✓ (post)

### Trial Procedures

The ProACT technology, described earlier and in Table 1, will be deployed to trial arm 1 and 2 participants in their homes for 6 months. Participants will regularly use the measuring devices and ProACT CareApp to record and manage key health and well-being parameters. Depending on the device, data will be uploaded automatically to the CareApp via Wi-Fi or Bluetooth or entered manually via the CareApp. An Internet connection will be provided to participants who do not have an existing connection in their homes. The technology will be withdrawn at the end of the trial, which will be clearly communicated beforehand and outlined in the consent form and PILs.

Care network participants will be asked to use the CareApp to view data shared by the participants with multimorbidity and to engage with the provided education materials. More specifically, the CareApp interface for each care network participant will allow the user to view the health and well-being data and medication details of participants with multimorbidity. Informal caregivers and formal caregivers will also receive educational material that pertains to the conditions of the participants with multimorbidity that they care for. Care network participants will be able to use the ProACT CareApp at a time and with a frequency that is convenient to them. The aim is to explore their experiences of technology and its perceived usefulness in supporting people with multimorbidity.

For trial arm 1, a clinical triage service in each country will review participants’ vital signs and alerts at least 5 days a week (Monday to Friday). Triage nurses may adjust personalized thresholds and will contact participants if alerts are triggered, to discuss the alerts, and to determine if further action is required. For instance, the participants will be encouraged to bring their CareApp to their health care visits (eg, in situations where a health care professional has not consented to participate in the trials); where a health care professional has consented to participate, they will be able to view the relevant data in their CareApp, including detailed weekly data across all health and well-being parameters.

The clinical triage services will also support the development and personalization of data collection plans for participants in trial arm 1. Prior to the trial, the research and triage teams will create a ProACT data collection plan “care plan” (for data collection only rather than for clinical or treatment purposes) for participants in trial arm 1, tailored to their conditions (eg, how often they should measure their symptoms). As the trial progresses, the clinical triage services, in consultation with participants, will personalize their data collection plans. Participants can access their plans through their CareApp and share them with those in their care network.

### Sample Size Justification

We used a 3-group comparison (ie, trial arms 1, 2, and 3) as the main fixed effect for a repeated measures ANOVA model to determine the sample size of the p-RCT. For a desired power of 0.80, an error variance of 2, and a type I error rate of 0.05 with an attrition rate of 30%, we estimated that we need 76 participants per arm per trial site (rounded up to 80) to detect a standardized effect size (Cohen *d*) of 0.25. In the situation that recruitment targets have been met and more participant candidates can be included in the study, we will aim for a sample size of 100 per arm per trial site instead of 80 to obtain a power of 0.90. Sample size and power analysis were conducted using STATA (version 17.0; StataCorp LLC).

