#### Person With Multimorbidity Participants

All participants will complete baseline questionnaires capturing their demographic, QoL, health, psychological and psychosocial, HCU, and multimorbidity self-management information (Table S1 in Multimedia Appendix 2) [39-48]. To reduce participant burden, questionnaires can be completed over 10 days. Data will be collected and managed using REDCap (Research Electronic Data Capture) software [49,50], hosted at Vrije Universiteit Brussel. Data collection mode will depend on participant preference. Those comfortable with technology will receive an email link; others will receive paper questionnaires, returned by post or collected during home visits for technology deployment (trial arms 1 or 2). Researchers may assist participants during these visits. For trial arm 3 participants, assistance will be provided via phone or online call, with researchers recording responses. When calls are not possible, a home visit will be arranged. Up to 60 participants in each of trial arms 1 and 2 (20 per country in Ireland, Belgium, and Sweden) will also take part in qualitative interviews to capture baseline information on current self-management strategies and trial expectations. Interview themes are detailed in Table S2 in Multimedia Appendix 2, while the T1 interview protocol is outlined in Multimedia Appendix 3. Interviews will be audio-recorded, transcribed, annotated, and analyzed.

All participants will complete QoL and HCU questionnaires at trial start (T1) and end (T2). As HCU is a key outcome, participants will report monthly to improve recall with data captured through REDCap either online or via researcher-assisted calls.

At trial completion, participants will again complete questionnaires (Table S1 in Multimedia Appendix 2), within a 10-day period, but if extenuating circumstances exist (eg, if participants are on holiday), within a 4-week period. Semistructured interviews with up to 60 participants in each of trial arms 1 and 2 will explore experiences using ProACT, self-management strategies, symptoms, and care network roles (themes in Table S2 in Multimedia Appendix 2, full interview protocol in Multimedia Appendix 4).

System use data (eg, technology engagement metrics and health data from sensors) and triage service use (eg, call frequency) will be continuously collected through the ProACT platform throughout the 6-month trial (Table S2 in Multimedia Appendix 2).

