### Data Analysis Plan

For the p-RCT primary outcomes, three types of analysis will be conducted: (1) What is the influence of ProACT on perceived QoL? (2) What is the influence of ProACT on HCU? (3) What trial arm is the most cost-effective?

To determine if significant differences exist in (1) perceived QoL between the arms and (2) HCU between the arms, a linear mixed model will be used. In this model, a 2-level structure will be applied; repeated measures of QoL or HCU will comprise the first level, and participants will comprise the second level in the hierarchy. The outcomes will be assessed longitudinally using fixed effects of time, treatment arm and time interaction, and other baseline covariates such as age and gender.

ProACT’s cost-effectiveness will be determined with the use of 2 economic evaluation techniques, cost-effectiveness standard and cost-utility analysis, applying the societal perspective. Societal perspective means, in general terms, the effectiveness evaluation will consider all the relevant contributors related to the participant. The 2 methods will allow the determination of the monetary value and the benefits of the intervention in health terms. For the monetary value, the HCU data will form the basis of the analysis.

Due to the questionnaire construction variation (countable and binary questions) and the time points of data collection during the trial, the analysis will make use of 3 statistical models: Poisson (countable data), logistic (binary response data), and linear regression (continuous data). The analysis will allow the observation of how ProACT affects the HCU, per arm at each trial site, and what the costs involved in this effect are for the monetary value definition. To define a 95% CI for this cost-effectiveness estimate per arm and per trial site, a sensitivity analysis will be performed, for instance, using a bootstrapping methodology.

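### For QoL, the stated power belongs to an arm main effect that averages in the baseline, while the planned analysis is built on an arm-by-time interaction

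*Protocol article*

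**What the plan says.** The Sample Size Justification describes the test that was sized: "We used a 3-group comparison (ie, trial arms 1, 2, and 3) as the main fixed effect for a repeated measures ANOVA model". Its inputs are "For a desired power of 0.80, an error variance of 2" and "a type I error rate of 0.05 with an attrition rate of 30" percent, and the target is "to detect a standardized effect size (Cohen *d*) of 0.25". The result is "we estimated that we need 76 participants per arm per trial site (rounded up to 80"), with an option for more: "we will aim for a sample size of 100 per arm per trial site instead of 80 to obtain a power of 0.90".

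The Data Analysis Plan compares the arms on QoL and on health care use (HCU) with a two-level linear mixed model that has "fixed effects of time, treatment arm and time interaction, and other baseline covariates such as age and gender".

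The section on participants with multimorbidity fixes the measurement times: "All participants will complete QoL and HCU questionnaires at trial start (T1) and end (T2"). HCU is also reported monthly; QoL is not. T1 precedes the intervention.

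**The concern.** With one measurement before and one after the start of treatment, the arm main effect and the arm-by-time interaction are different tests. The main effect compares each participant's average of T1 and T2. Randomised arms have no expected difference at T1, so that average carries only half of any difference present at T2. The interaction compares the change from T1 to T2, so it carries the whole T2 difference, with a different variance.

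The 0.80 and 0.90 are stated for the first test, and the analysis model is built on the second. A reader cannot tell what power the planned QoL analysis has. A borderline QoL result could also be significant on one term and not on the other. Both the sizing contrast and the model terms are in the article itself, so this is a mismatch between two statements and not merely detail left for a later plan.

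**Working it through.** **Inputs.** From the Sample Size Justification: three equal arms, type I error 0.05, power 0.80, attrition 30%, effect 0.25, error variance 2. Assumed here: a T1-T2 correlation r of 0.3 to 0.8, since none is stated; equal variance at both occasions; complete pairs.

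**Step 1: reproduce the plan's figures.** For a between-participant F test with three groups and n completers per arm, the noncentrality is λ = f² × 3n, with 2 and 3n − 3 degrees of freedom.

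- f = 0.25, n = 53: λ = 0.0625 × 159 = 9.94, power 0.805. Then 53/0.70 = 75.7, so 76, as stated.
- 100 enrolled leaves 70: λ = 0.0625 × 210 = 13.1, power 0.907, against the stated 0.90.
- With 0.25 taken as Cohen d, the omnibus test needs 233 to 310 completers per arm (333 to 443 enrolled), depending on how the three means are spread. So 0.25 acts as Cohen f.
- The error variance of 2 also fits if the two occasions are uncorrelated: the variance of the average is 2/2 = 1, and an SD of arm means of 0.25 gives f = 0.25. With error variance 2 and r > 0, f falls to 0.25/√(1 + r), and even for an effect on the average the power is 0.69 at r = 0.3 and 0.54 at r = 0.8.

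**Step 2: place the effect at T2.** Let the arm difference be 0 at T1 and δ at T2, with single-occasion variance σ².

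- Main effect: difference δ/2, variance σ²(1 + r)/2. Noncentrality relative to a T2-only test: 0.25/((1 + r)/2) = 1/(2(1 + r)).
- Arm-by-time (with complete pairs, a test on change): difference δ, variance 2σ²(1 − r). Relative noncentrality: 1/(2(1 − r)).
- Ratio of interaction to main effect: (1 + r)/(1 − r), which is 3 at r = 0.5.

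**Step 3: power for a T2 effect of f = 0.25 in single-occasion SD units.** The pooled column uses 80 × 0.70 = 56 completers per arm per site, times 3 = 168.

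| r | Main effect, 53 per arm (one site) | Arm-by-time, 53 per arm | Main effect, 70 per arm | Main effect, 168 per arm (pooled) | Arm-by-time, 168 per arm |
|---|---|---|---|---|---|
| 0.3 | 0.39 | 0.65 | 0.50 | 0.88 | 0.99 |
| 0.5 | 0.35 | 0.81 | 0.44 | 0.83 | 1.00 |
| 0.7 | 0.31 | 0.96 | 0.40 | 0.78 | 1.00 |
| 0.8 | 0.29 | 1.00 | 0.38 | 0.76 | 1.00 |

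**Step 4: what the main effect needs to have its stated power.** The effect on the T1-T2 average must itself be 0.25, so the raw arm difference at T2 must be twice that. In single-occasion SD units this is f = 0.5 × √((1 + r)/2), or 0.40 at r = 0.3 and 0.47 at r = 0.8.

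**The case against.** A reader might infer that the sized test lacks its stated power, or that the trial is underpowered. The documents support neither.

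- On the inputs that reproduce 76, the main effect has 0.805, and 0.907 at 100 per arm. The article never says that 0.25 is an effect at T2 alone. This stands. The shortfall in Step 3 concerns a T2 effect of f = 0.25, which is the natural reading for a randomised before-and-after QoL measure but is an assumption.
- The planned interaction has more power than the main effect for any positive correlation. It reaches 0.80 per site at r of about 0.5. This stands.
- The figure of 76 does not by itself identify the main effect. At r = 0.5 the interaction multiplier is 1/(2 × 0.5) = 1, so it too needs 53 completers, and the article's phrase could loosely mean the principal factor in the model. This stands as arithmetic. But no correlation is given, and the wording names the arm comparison, so the reader would have to guess.
- The QoL model is not described as fitted by site. Pooled, even the main effect has 0.76 or more. This stands, although the sample size is stated per site.
- HCU is also a primary outcome and is reported monthly, so the halving does not carry over to it. This stands; the point is confined to QoL.
- Naming the deciding term is often left to the analysis plan. This stands for that omission alone. It does not cover a power figure stated for one contrast beside a model built on another.
- The model phrase can also be read as listing arm as a separate term. That leaves both tests open and does not remove the mismatch.

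**Conclusion.** The point holds for QoL, in a limited form. The stated 0.80 and 0.90 belong to the arm main effect over T1 and T2, whereas the planned model estimates the treatment effect through arm-by-time. The main effect has the stated power only if 0.25, as Cohen f, is the effect on the T1-T2 average.

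For the same f at T2, the two tests differ widely per site: below 0.40 throughout for the main effect, and between 0.65 and 1.00 for the interaction. The gap narrows when sites are pooled. These figures rest on the assumed correlation range, equal variances and complete pairs.

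The error lies in which test the power statement describes. It is not evidence that the planned analysis is too small. Whether 0.25 should be labelled d or f is a separate matter, to be settled when the figure is restated.

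**What to change.** In the Sample Size Justification, restate the QoL power for the arm difference at T2, that is, the arm-by-time contrast of the Data Analysis Plan. Give the assumed T1-T2 correlation, the effect-size metric, and whether the figure is per site or pooled. In the Data Analysis Plan, state that the arm main effect over T1 and T2 is not the test of treatment effect on QoL.

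The cost is wording in two paragraphs and one rerun of the power calculation. Enrolment does not change; the article reports that recruitment has ended in all three countries. The change should be made before the QoL outcome is analysed. The downside is that the restated per-site power falls below 0.80 if the assumed correlation is below about 0.5 (0.65 at 0.3 with 53 completers per arm).

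### The 76 per arm per site matches Cohen f = 0.25, not the printed Cohen d = 0.25, so the stated per-site power of 0.80 or 0.90 for d = 0.25 does not hold as written

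*Protocol article*

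**What the plan says.** The sizing rests on a "3-group comparison (ie, trial arms 1, 2, and 3) as the main fixed effect for a repeated measures ANOVA model". Its inputs are "For a desired power of 0.80, an error variance of 2", "a type I error rate of 0.05" and attrition of 30%. The result is given per site: "we need 76 participants per arm per trial site (rounded up to 80) to detect a standardized effect size", named as Cohen d, of 0.25. An optional extension follows: "we will aim for a sample size of 100 per arm per trial site instead of 80 to obtain a power of 0.90". The paragraph gives no number of repeated measures, no within-person correlation and no pattern of arm means.

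Elsewhere in the article, the p-RCT Methodology overview gives 80 per arm in each country and 240 per arm overall. The Data Analysis Plan uses a linear mixed model with "fixed effects of time, treatment arm and time interaction, and other baseline covariates such as age and gender".

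**The concern.** In a 3-group F test the natural effect size is Cohen f, the SD of the arm means divided by the within-arm SD. Cohen d is a difference between two means. For the same arms f is less than half of d, so swapping the labels changes the required number several-fold. A requirement of 76 per arm, attrition included, is far too small for d = 0.25 on a single measure, and it is exactly the textbook figure for f = 0.25.

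Recruitment has finished and outcomes are due for publication in 2026, so what is at stake is interpretation. A reader who meets a null result, above all within one country, would take it as evidence against effects of 0.25 SD at 80% or 90% power. The printed inputs do not support that inference.

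**Working it through.** **Inputs from the Sample Size Justification:** 3 equal arms, alpha 0.05, power 0.80 (0.90 for the extension), attrition 30%, effect size 0.25. **Assumed, because not stated:** the pattern of arm means and the within-person correlation rho; both are varied below.

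**Method.** Omnibus F test with df 2 and N − 3, noncentrality N × f² / v. Here N is the total number of completers and v is a variance factor: 1 for a single measure, (1 + rho)/2 for an arm main effect averaged over two times, and 1 − rho² for a baseline-adjusted analysis. Enrolled = completers / 0.70.

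**Step 1: reproduce the plan's figure.** With f = 0.25 and v = 1:
- 52 completers per arm give power 0.797 and 53 give 0.805. 53/0.70 = 75.7, so 76, as printed.
- For power 0.90, 69 completers are needed. 69/0.70 = 98.6, so 99. With 100 enrolled, 70 complete and power is 0.907.

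**Step 2: what f = 0.25 means between arms.** If the third mean lies midway, d = f × √6 = 0.25 × 2.449 = 0.61. If two means are equal, d = f × 3/√2 = 0.25 × 2.121 = 0.53.

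**Step 3: what d = 0.25 needs.** Taken as the largest difference between arms, d = 0.25 gives f = 0.25/√6 = 0.102 (third mean midway) or f = 0.25 × √2/3 = 0.118 (two means equal).
- Single measure: 310 or 233 completers per arm, so 443 or 333 enrolled.
- Arm main effect over two measures at rho = 0, its most favourable non-negative value (v = 0.5): 156 or 117 completers, still not 53.
- One pairwise t test, single measure: 253 completers, 253/0.70 = 361.4, so 362 enrolled.
- Treating 0.25 as a raw difference with variance 2 moves further away: 503 per arm for one pairwise comparison.

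**Step 4: power at d = 0.25** (ranges run over the two patterns of means). Per-site completers are 80 × 0.70 = 56 and 100 × 0.70 = 70. Pooled completers at 80 per site are 240 × 0.70 = 168.

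| Completers per arm | v = 1 | Baseline-adjusted, rho 0.5 | rho 0.6 | rho 0.7 |
|---|---|---|---|---|
| 56 (one site, 80 enrolled) | 0.20–0.25 | 0.25–0.33 | 0.29–0.38 | 0.36–0.46 |
| 70 (one site, 100 enrolled) | 0.24–0.31 | 0.31–0.40 | 0.36–0.46 | 0.44–0.56 |
| 168 (three sites pooled) | 0.52–0.65 | 0.65–0.78 | 0.73–0.85 | 0.82–0.92 |

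**Step 5: detectable difference for a pooled pairwise contrast.** With 168 completers per arm and 80% power it is 0.307 SD unadjusted. Multiplying by √(1 − rho²) gives 0.265, 0.245 and 0.219 SD at rho 0.5, 0.6 and 0.7.

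**The case against.** The best defence is that the stated model has repeated measures and its correlation is not given, so d = 0.25 is not excluded. This has force. Pooled over the three sites, d = 0.25 yields 76 per arm per site at rho of about 0.03 to 0.37 (two-time main effect), 0.56 to 0.70 (baseline-adjusted) or 0.66 to 0.74 (change score). A reader might therefore infer too much in saying that the number can arise only from f = 0.25; the document does not establish that. The match with f also sets aside two stated features. It makes no use of the error variance of 2, and it ignores the repeated measures: with two of them, f = 0.25 needs only 40 completers (58 enrolled) at rho 0.5 and reaches 53 only at rho = 1.

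Nor is the figure of 100 for power 0.90 a second confirmation. Going from 0.80 to 0.90 multiplies the number by about 1.3 at any effect size here (69/53 = 1.30; 406/310 = 1.31), so 76 becomes about 100 under either label.

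The defence does not rescue the sentence as printed. The paragraph names an arm main effect and counts participants per arm per trial site. On that basis no non-negative rho gives 76 at d = 0.25 for the two-time main effect, and a baseline-adjusted or change analysis would need rho of about 0.88 to 0.92.

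Another tempting reading is that the whole trial has power of only 0.2 or so for 0.25 SD. The documents do not support that either. The mixed model for the primary outcomes is not said to be run site by site, and pooled power with a moderate correlation lies around the claimed level. Finally, sizing on an arm effect while testing arm by time is a common simplification; its direction depends on rho, and on its own it would be a minor point.

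**Conclusion.** The concern holds for the printed claim: d = 0.25, per arm per site, power 0.80 or 0.90. The effect-size label is very likely wrong, although that is an inference from an exact numerical match and not proof. If 0.25 is f, the design was sized per site for differences more than twice as large as stated.

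At d = 0.25, single-site power falls far short of the stated values on every assumption tried in the table, including baseline adjustment at rho up to 0.7. For the pooled comparison the shortfall is not shown. Without adjustment, power is below 0.80; with baseline adjustment, whether it reaches 0.80 depends on a correlation that would have to be stated. These figures assume exactly 30% attrition, equal arms, d as the largest difference between arms, and the omnibus F test. The error touches how results are read, not how the trial is conducted.

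**What to change.** Go back to the Stata calculation and correct the effect-size metric to whichever was used, f or d; f should not be printed on the strength of this check alone. State in the same paragraph the number of measures, the assumed correlation, and whether the calculation is per site or pooled.

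Then restate the power, or the detectable difference at 80% power, for the analysis that will be run: the mixed-model arm-by-time contrast pooled over sites. With 168 completers per arm that is about 0.31 SD unadjusted, or about 0.27 to 0.22 SD if baseline is adjusted for and rho is 0.5 to 0.7. Add that comparisons within a single site do not have power 0.80 or 0.90 for 0.25 SD.

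The cost is one reworded paragraph and a less favourable stated figure per site. No further participants are needed.
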